## Abstract

**Background:**

One in five patients with ischaemic heart disease (IHD) develop comorbid depression or anxiety. Depression is associated with risk of non-adherence to cardiac rehabilitation (CR) and dropout, inadequate risk factor management, poor quality of life (QoL), increased healthcare costs and premature death. In 2020, IHD and depression are expected to be among the top contributors to the disease-burden worldwide. Hence, it is paramount to treat both the underlying somatic disease as well as depression and anxiety. *eMindYourHeart* will evaluate the efficacy and cost-effectiveness of a therapist-assisted eHealth intervention targeting depression and anxiety in patients with IHD, which may help fill this gap in clinical care.

**Methods:**

*eMindYourHeart* is a multi-center, two-armed, unblinded randomised controlled trial that will compare a therapist-assisted eHealth intervention to treatment as usual in 188 CR patients with IHD and comorbid depression or anxiety. The primary outcome of the trial is symptoms of depression, measured with the Hospital Anxiety and Depression Scale (HADS) at 3 months. Secondary outcomes evaluated at 3, 6, and 12 months include symptoms of depression and anxiety (HADS), perceived stress, health complaints, QoL (HeartQoL), trial dropout (number of patients dropped out in either arm at 3 months) and cost-effectiveness.

**Discussion:**

To our knowledge, this is the first trial to evaluate both the efficacy and cost-effectiveness of a therapist-assisted eHealth intervention in patients with IHD and comorbid psychological distress as part of CR. Integrating screening for and treatment of depression and anxiety into standard CR may decrease dropout and facilitate better risk factor management, as it is presented as “one package” to patients, and they can access the *eMindYourHeart* program in their own time and at their own convenience. The trial holds a strong potential for improving the quality of care for an increasing population of patients with IHD and comorbid depression, anxiety or both, with likely benefits to patients, families, and society at large due to potential reductions in direct and indirect costs, if proven successful.

*Trial registration* The trial was prospectively registered on https://clinicaltrials.gov/ct2/show/NCT04172974 on November 21, 2019 with registration number [NCT04172974].

## Background

Ischaemic heart disease (IHD) is a chronic disease, characterised by reduced blood supply to the heart due to the build-up of plaque in the coronary arteries that may lead to a heart attack – an acute myocardial infarction (AMI). The number of patients living with IHD has increased exponentially due to ageing of the population and more patients surviving due to better treatment options [1]. In Denmark alone, 21,000 new patients are diagnosed with IHD every year [2].

An AMI often comes out of the blue and comprises a threat to the patient’s life and sense of self. The sudden confrontation with a life-threatening illness may trigger different psychological responses. Not surprisingly, 20% of patients suffer from depression, anxiety or both [3]. Both a clinical diagnosis and subthreshold levels – often undetected – comprise barriers for lifestyle changes, increase risk of non-adherence, refusal *or* dropout from cardiac rehabilitation (CR), hospitalisation, and premature death [4–6]. The health economic impact associated with both IHD [7] and depression [8, 9] are high. Depression alone adds an extra cost of 33% compared to patients without depression [10]. Compounding the issue, both IHD and depression are among the top contributors to the disease-burden worldwide in 2020 [2, 11, 12], warranting that we treat both the underlying somatic disease and psychological comorbidity [13].

In order to mitigate the impact of IHD, national guidelines on CR have been implemented across the world. CR is a multi-disciplinary effort targeted to reduce progression of heart disease. The focus is on improving the patient’s functional level physically, mentally and socially, reducing activity-related symptoms, minimising disability, and improving QoL [14, 15]. There may be variability in programs. Evidence for an effect of CR is strong with significant reduction in mortality on top of state-of-the-art treatments, such as percutaneous coronary intervention and pharmacotherapy [16]. However, to obtain these benefits, it is paramount that patients are offered CR, consent to participate, and stay in the program. So far there is still room for improvement with respect to retention [17]. Numerous barriers for participation and adherence exist and include person-related factors (e.g. gender, socio-economic status, health literacy, and comorbidities), factors related to the CR program (e.g. accessibility, proximity to the CR setting) [18], and anxiety and depression [5, 18].

In 2013, the Danish Health Authority included screening for symptoms of depression and anxiety with the Hospital Anxiety and Depression Scale (HADS) in the national clinical guidelines on CR [19]. However, the CR setting has no treatment to offer patients who screen positive, except referring them to their general practitioner (GP). The Danish situation is not unique, as screening combined with treatment of patients’ distress is far from universally implemented [20].

### eHealth and its potential in the cardiac rehabilitation setting

*eMindYourHeart* represents an innovative solution to bridge this gap in clinical care [17], as it introduces a tailored therapist-assisted eHealth intervention targeting depression and anxiety that is added to standard CR. Internet-delivered treatment for common mental disorders has been investigated in well over 100 randomised controlled trials (RCTs) and are as effective as face-to-face-treatment [21–24]. Advantages of internet-delivered treatment include that patients can access the intervention anytime from anywhere, work at their own pace, and avoid taking time off work to see a psychologist. This may reduce barriers for engaging in treatment as part of CR [25] and societal costs, since patients do not need to take time off work. Due to the flexibility of the mode, it may also be more easy for patients to integrate treatment into their daily lives [26]. An online treatment approach also secures continuity of treatment for patients even during pandemics like COVID-19, when hospitals largely close down for patients with less acute needs.

Only few studies [27–29] have examined the efficacy of an approach like *eMindYourHeart* to treat compromised mental health in patients with IHD, with the studies showing mixed results. Two studies delivered such intervention in addition to traditional CR [30]. To our knowledge, no studies have examined both the efficacy and cost-effectiveness of such interventions in patients with IHD referred to CR. High quality studies are warranted due to the current moderate quality level of trials in this field [30]. These programs should not be one-size-fits-all but targeted to the individual patient’s needs and preferences [17].

### Objectives and hypotheses

#### Primary objective

The primary objective is to evaluate the efficacy of the eHealth intervention *eMindYourHeart* targeting depression and anxiety + treatment as usual (TAU) (i.e. current CR) as compared to TAU alone on symptoms of depression at 3 months (end of the intervention). We chose TAU as the comparator, as we want to examine whether our intervention improves patients’ depression and anxiety outcomes. We chose depression as the primary outcome, as evidence on depression as a risk factor for mortality is more solid than evidence on anxiety [31].

#### Secondary objectives

The secondary objectives are to evaluate the efficacy of the eHealth intervention targeting depression and anxiety + TAU as compared to TAU alone on symptoms of anxiety, perceived stress, health complaints, QoL, and dropout (number of patients dropped out in either arms at 3 months) at 3 months, and symptoms of depression, anxiety, perceived stress, health complaints, and QoL at 6 and 12 months’ follow-up and cost-effectiveness/cost-utility.

#### Hypotheses

Given the user-centered, therapist-assisted eHealth approach to treat depression and anxiety, allowing patients to engage in the intervention when and where they want, we hypothesise that the intervention will be broadly acceptable to patients, have a low dropout rate and be effective and cost-effective.

## Methods

### Trial design

*eMindYourHeart* is a multi-center, two-armed, unblinded, parallel group RCT (see Fig. 1**)**. The trial will enroll patients from the CR settings at hospitals and municipalities delivering CR across all five regions in Denmark. We will use the TIDieR (Template for Intervention Description and Replication) guidelines and the CONSORT eHealth Checklist when reporting the results of the *eMindYourHeart* RCT [32, 33].

**Fig. 1 Fig1:**
[figure not shown]
Trial design and flowchart of patient inclusion and follow-up

### Eligibility and recruitment

Consecutive patients referred to CR with IHD, ≥18 years of age, with a diagnosis of IHD (codes I20-I25), HADS score ≥ 8 on depression, anxiety or both, with access to a computer or smartphone, ability to use a computer or smartphone, and proficient in the Danish language are eligible for inclusion. Patients with severe psychiatric disorders (i.e., borderline disorder, schizophrenia or bipolar disorder), severe cognitive difficulties (e.g. severe brain damage, mental retardation, or dementia) that will prevent patients from participating, endorsement of suicidal ideation with daily suicidal thoughts (PHQ-9 item 9 > 2), participating in other intervention studies (unless they are clinical studies [e.g. medication trials]), or seeing a psychologist or mental health professional for the treatment of depression and anxiety, will be excluded (Fig. 1). Patients who were previously enrolled in the study and referred to CR due to a new cardiac event will not be eligible to participate a second time. Table 1 presents an overview of the recruitment procedure.

**Table 1 Tab1:** Overview of recruitment procedure

• Patients will be recruited consecutively from the participating CR centres. • When the patient first visits the CR centre, one of the members of staff will screen the patient for symptoms of depression and anxiety. • If the patient has a positive score on depression and/or anxiety and complies with the additional inclusion criteria and none of the exclusion criteria, CR staff will inform the patient orally and in writing about the study. • Two scenarios are then possible: 1. If the patient is interested in participating in the study and does not wish additional time to contemplate the decision or to have a significant other present, informed consent will be signed by both parties. 2. If the patient is interested in participating in the trial and wishes either 24 h to contemplate the decision and/or to have a significant other present, they receive a link to a declaration of consent via e-boks. • After having signed the informed consent (the patient will receive a copy) the patient will be included into the study. • A note will be added to the patient’s electronic health records, if the patient is included into the study. • A link to the questionnaire to complete at baseline will be sent to the patient via e-boks. • When the therapist has received a confirmation that the questionnaire has been completed, and if the HADS score is still positive, the patient will be contacted by telephone by the therapist and take part in a short purpose-designed diagnostic interview. • Within 2 days, eligible patients are randomised to either TAU *or* TAU + the *eMindYourHeart* intervention by administrative staff from SDU and informed of the result by the therapist. • Patients allocated to TAU + the *eMindYourHeart* intervention will receive instructions on how to use/access the platform by the therapist. • Patients who do not wish to participate in the study are asked about *(i)* the reason and *(ii)* whether we may use the patient’s data from the rehabilitation settings and DHDR.	

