## Sample size calculation

Based on Stauber et al. [34], a conservative estimate of the standard deviation of the mean of the HADS depression score at 3 months is 3.5. The minimal clinically important difference for the HADS is 2 points [35]. For a normal-based comparison of independent means, with a power of 90% (ß = 0.1) and a risk of Type 1 error of 5% (α = 0.05), the estimated required number of patients is *n* = 66 in each group. Considering a potential 30% dropout rate, the estimated number of needed participants is *n* = 94 patients in each group (n (total) = 188).

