## Trial outcomes

Primary: Symptoms of depression, measured with HADS at the end of the intervention (i.e., 3 months).

Secondary: Symptoms of anxiety measured with HADS at 3 months; symptoms of depression and anxiety at 6- and 12 months’ follow-up; QoL (HeartQoL) at 3, 6, and 12 months follow-up; trial dropout (number of patients dropped out in either arms at 3 months) and cost-effectiveness/cost-utility.

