## Statistical methods

Data will be analysed according to the modified intention-to-treat principle (i.e., all patients with a 3-month evaluation will be analysed as randomised). The intention-to-treat principle will be applied from the time that patients have initiated treatment (i.e., after the brief interview protocol that includes elements from the SCAN interview and motivational interviewing). Categorical variables will be summarised as n (%), continuous variables as min-max, mean (SD), and median. All summaries will be by randomisation group. The primary analysis will be a linear regression of depression scores at 3 months including randomisation group and strata as factors and baseline depression scores as covariate. Potential confounders, apart from baseline and stratification variables, identified by clinical consensus, will be included in multivariable analyses when appropriate (e.g. when performing sub-group analyses). A mixed effects model will be used to analyse the longitudinal change in HADS scores and HeartQoL scores, adjusting for strata, incorporating random effects to model the homogeneity within cluster and the correlation within patient across time. Pre-planned subgroup analyses will be conducted for the primary outcome with respect to: *(i)* type of IHD (stable versus unstable); *(ii)* sex (female versus male); *(iii)* age (median split); *(iv)* depression status at baseline (< 10 versus ≥11; *≥11 is considered a moderate score*). A sensitivity analysis will be conducted. The statistical analysis will be transparent, subject to review and approval by the project team.

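### The planned baseline-depression subgroup (below 10 versus 11 or more) does not fit a trial that admits patients on anxiety alone: it straddles the entry threshold of 8 and leaves a score of 10 unassigned

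*Protocol article*

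**What the plan says.** The protocol article's Eligibility and recruitment section admits patients with "HADS score ≥ 8 on depression, anxiety or both". The check before randomisation (Table 1) sets no separate requirement for depression: "if the HADS score is still positive, the patient will be contacted by telephone by the therapist". The outcome is specific to depression: "Primary: Symptoms of depression, measured with HADS at the end of the intervention (i.e., 3 months". The Primary objective section gives the reason: "We chose depression as the primary outcome, as evidence on depression as a risk factor for mortality is more solid than evidence on anxiety".

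The Sample size calculation applies one difference to the whole sample, "The minimal clinically important difference for the HADS is 2 points", and makes no allowance for patients who enter on anxiety alone. Randomisation is stratified by site and by stable versus unstable disease, not by baseline depression.

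Under Statistical methods, the primary regression adjusts for the baseline depression score; no treatment-by-baseline term is stated. One of the four pre-planned subgroup analyses of the primary outcome concerns "depression status at baseline (< 10 versus ≥11; *≥11 is considered a moderate score".

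**The concern.** A patient with a HADS anxiety score of 12 and a HADS-D of 3 is eligible and counts fully in the primary comparison, but has little room for a 2-point fall in HADS-D. If there are many such patients, the average effect could be smaller than the effect in patients who screened positive for depression. A reader faced with a small or null primary result would then want to know the effect above and below the trial's own depression threshold.

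The subgroup on baseline depression is the natural place to look, but its boundaries do not answer that question. The threshold of 8 appears in no stated analysis. A cut chosen after a null result would carry little weight, so the right boundary should be fixed in advance.

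**Working it through.** **1. The stated categories against the entry threshold** (HADS-D taken as whole numbers, as the stated cuts imply)

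| Baseline HADS-D | Screen-positive for depression (8 or more)? | Planned subgroup |
|---|---|---|
| 0–7 | No; entered on anxiety | Lower |
| 8–9 | Yes | Lower |
| 10 | Yes | Neither |
| 11 or more | Yes | Upper |

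The lower group pools two populations, one score is unassigned, and only the upper group is purely screen-positive for depression. Patients scoring 8 to 10 are nowhere estimated apart from anxiety-only patients.

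**2. The plan's sample size.** Inputs from the Sample size calculation: difference 2, SD 3.5, "with a power of 90% (ß = 0.1) and a risk of Type 1 error of 5% (α = 0.05". Sidedness is not stated; two-sided is assumed.

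- Normal formula: n = 2 × [3.5 × (1.960 + 1.282) / 2]² = 64.4, so 65 per group.
- t-test: 65.3, so 66 per group, as stated. Power at 66 is 90.3%.
- Dropout: 66 / 0.70 = 94.3. The plan gives 94, total 188.

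The figure reproduces. It holds if the mean effect over all analysed patients, including anxiety-only entrants, is 2 points.

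**3. Possible dilution.** Let p be the share with baseline HADS-D below 8 and e their effect. The protocol gives neither, so both are assumptions, as is a 2-point effect at 8 or more. Mean effect = 2(1 − p) + e·p. Two-sided t-test at 66 per group, SD 3.5, e = 0.5:

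| p | Mean effect | Power, unadjusted |
|---|---|---|
| 20% | 1.6 + 0.10 = 1.70 | 79% |
| 30% | 1.4 + 0.15 = 1.55 | 71% |
| 40% | 1.2 + 0.20 = 1.40 | 63% |

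The choice of e matters. By the normal approximation (about a point higher than the t-test), the same shares give 75%, 63% and 50% with e = 0, and 84%, 80% and 75% with e = 1.

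**4. Effect of the planned baseline adjustment.** With baseline-to-outcome correlation r, the residual SD is 3.5 × √(1 − r²): 3.21 at r = 0.4 and 2.80 at r = 0.6 (r is assumed). For e = 0.5, power becomes about 86–93%, 79–88% and 70–81% for shares of 20%, 30% and 40%. Adjustment recovers power but leaves the mean effect at 1.70, 1.55 and 1.40 points.

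**5. What the upper group can show.** If 20% to 50% of patients score 11 or more (assumed), there are 13 to 33 per group. The 95% CI half-width, 1.96 × 3.5 × √(2/n), is 2.7 to 1.7 points, and power for 2 points is about 31% to 64% (normal approximation).

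**6. What a cut at 8 would show.** With 66(1 − p) = 52.8, 46.2 and 39.6 per group at 8 or more, the unadjusted t-test has power of about 83%, 78% and 71% for 2 points. The half-width is about 1.3, 1.4 and 1.5 points, against 1.2 in the full sample. This estimate is much more precise than that of the upper group as now defined.

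**The case against.** The strongest reply is that mixed entry is intended. The intervention targets depression and anxiety, the trial population is described throughout as having either or both, the choice of depression as the single primary outcome is explained, and HADS anxiety at 3 months is a named secondary outcome. The average effect on depressive symptoms in screen-positive rehabilitation patients is a coherent quantity to estimate. This stands, and there is no case for changing entry or the primary analysis.

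A reader might infer that a null result could not be interpreted for depressed patients at all. The protocol does not support that. The group at 11 or more contains no anxiety-only patients, and an effect there but not in the lower group would point to dilution.

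A reader might also infer that the trial is underpowered. That is not shown: the power figures rest on an assumed share and an assumed effect, and they leave out the planned covariate. The protocol also calls its SD conservative: "a conservative estimate of the standard deviation of the mean of the HADS depression score at 3 months is 3.5".

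Nor does the protocol say that anxiety-only patients receive less depression-directed work. The section on treatment adherence says only that exposure work is likely not relevant for a patient whose main problem is depression.

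Finally, supportive analyses are often left to an analysis plan, which is not shown here. That covers a missing extra analysis. It does not cover a cut that the article itself states, and that leaves a gap and straddles the entry threshold.

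**Conclusion.** The point holds as a defect in one pre-planned subgroup analysis. As written, its categories are not exhaustive and do not match the threshold by which patients enter, so no stated analysis estimates the effect in all patients with HADS-D of 8 or more or isolates those below 8. This follows from the text alone and needs no assumption.

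The size of any dilution cannot be fixed from the protocol. Under the 0.5-point assumption the primary comparison could have roughly 63% to 79% power unadjusted, and about 70% to 93% with baseline correlations of 0.4 to 0.6. These figures illustrate why the split is worth having; they do not demonstrate a shortfall. The subgroup calculations also assume that the SD of 3.5 carries over to each subgroup. The correction is worth making before allocation is unblinded, but the validity of the primary analysis does not depend on it.

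**What to change.** Keep enrolment and the primary analysis as they are. In Statistical methods, redefine the baseline-depression subgroup at the entry threshold: HADS-D below 8 versus 8 or more. If the moderate cut is still wanted, keep it as an additional one with no gap, for example bands of 0–7, 8–10 and 11 or more. Pre-specify the treatment-by-baseline-HADS-D interaction, with baseline as a continuous score, as a supportive analysis. State that these results are read alongside the primary result and do not replace it: the subgroups are not stratified at randomisation, and resting the conclusion on one of them would be hard to defend.

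The change is in wording only, because HADS-D is already collected at baseline and at the end of treatment (Table 3). The cost is one more subgroup result to report, with estimates less precise than that of the full sample.

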## Sample size calculation

Based on Stauber et al. [34], a conservative estimate of the standard deviation of the mean of the HADS depression score at 3 months is 3.5. The minimal clinically important difference for the HADS is 2 points [35]. For a normal-based comparison of independent means, with a power of 90% (ß = 0.1) and a risk of Type 1 error of 5% (α = 0.05), the estimated required number of patients is *n* = 66 in each group. Considering a potential 30% dropout rate, the estimated number of needed participants is *n* = 94 patients in each group (n (total) = 188).

## Ethics and safety considerations

Ethical approval for the trial is obtained from the Regional Committees on Health Research Ethics for Southern Denmark [S-20180024] (version 5 approved 10 September 2019). The required permissions are obtained from the Danish Data Protection Agency via Odense University Hospital (17/41433 on November 24, 2017). The trial will be conducted according to the Helsinki Declaration and was prospectively registered on http://www.clinicaltrials.gov [NCT04172974]. All patients will receive oral and written information about the trial and sign an informed consent form. Patients who do not wish to participate in the trial are asked about *(i)* the reason and *(ii)* whether we may use the patient’s data from the rehabilitation setting and the Danish Cardiac Rehabilitation Database (DHRD). DHRD is a Danish quality database that collates health data on CR from all hospitals in Denmark to ensure cohesiveness and quality in CR in Denmark [36]. It is compulsory for all hospitals offering CR to report into the database.

Subjects can leave the trial at any time for any reason if they wish without any consequences. The investigator can decide to withdraw a subject from the trial due to urgent medical reasons. Subjects withdrawn from the trial will not be replaced and will not be followed-up. Subjects who drop out of the trial will be followed up according to the intention-to-treat principle [37].

There are no expected medical risks associated with trial participation, as medical treatment is provided according to national clinical guidelines [14] and the trial compares two types of care (i.e., *(i)* TAU + eHealth intervention versus *(ii)* TAU. However, we cannot rule out that the eHealth intervention may induce additional depression and anxiety in some patients [38]. The Ethics Committee does not require us to have a Data Safety Monitoring Board (DSMB), but annually we are required to report serious side effects and incidents to the Committee.

The treatment manual developed for the trial includes guidelines for therapists how to handle patients scoring high on suicidal ideation. Patients with a Patient Health Questionnaire (PHQ-9 item 9) > 2 will be excluded from the trial and will be asked to see their general practitioner (GP) and can be referred to *Livslinien* (Danish suicidal prevention hotline). All other patients will be included. Therapists also administer the CORE-10 to patients several times during the intervention to evaluate progress (Fig. 2). In case of deterioration, a contingency plan as written into the treatment protocol will be implemented that includes e.g. more frequent contact, more tailoring to meet patients’ needs, suicidal risk assessment, referral to GP for evaluation of psychopharmaca etc.

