## Definition of treatment adherence and dropout

In internet-based therapy, research it is often unclear how treatment adherence is defined and there seems to be no gold standard [42]. However, use of different definitions across studies makes comparisons difficult with respect to efficacy of internet-based therapy. In *eMindYourHeart*, we define treatment adherence by the number of modules that the patient completes. Since treatment needs of individual patients may vary and we have elective modules that will be allocated to patients based on their needs, a module is considered completed, when the therapist judges that the individual patient has worked sufficiently with the exercises in the module. For example, if a patient primarily suffers from depression and not anxiety, the module focusing on exposure therapy is likely not relevant. The therapist’s judgement is made according to guidelines specified in the treatment manual. This ensures consistency across therapists and enhances the fidelity of the study.

A patient is considered a dropout, if the patient actively informs the therapist that the patient wishes to stop treatment. A patient who, at some point during treatment, stops adhering to treatment and does not respond to the therapist, will not be considered a dropout, but will stay enrolled in the treatment until the end of the 12-week treatment duration.

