## Other measures

Information on patients’ demographic and clinical characteristics at baseline will be captured from patients’ medical records at the rehabilitation centre *or* the hospital, DHRD*, or* via purpose-designed questions. These questions will be included in the questionnaire sent to patients at baseline with standardised and validated measures (Table 3).

Measures of total health care costs measured in EUR will be collected from the Danish administrative health care registers. Loss of labour market productivity will be calculated using the human capital approach where average wages are used to estimate loss of work productivity. Costs will be measured in 2020 prices using a currency rate of 1 EURO to 7.45 DKK. Health care costs include all hospital utilisation aggregated using the Danish diagnosis-related group (DRG) prices (somatic and psychiatric care). Primary care services will be aggregated using national health insurance service fees (including GPs and private practicing specialists). Total utilisation of prescription drugs will be measured by purchasing prices of the patient excluding value added tax (VAT).

Cost-utility will be measured by estimation of the incremental costs for a gain in QoL. Costs will be covering intervention costs and 12-month total health care utilisation. Thus, the cost-utility analysis will be carried out using the perspective of the health care sector. QoL will be measured using HeartQoL at 3, 6 and 12 months. A probabilistic approach will be used to assess uncertainty and acceptability curves will estimated.

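### Randomised patients whom the investigator withdraws on urgent medical grounds get no follow-up, so health-related events after randomisation decide who stays in the analysis

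*Protocol article*

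**What the plan says.** Under Ethics and safety considerations, the protocol article first allows patients to leave at any time. It then gives the investigator a separate power: "The investigator can decide to withdraw a subject from the trial due to urgent medical reasons". Two rules follow in consecutive sentences. The first is "Subjects withdrawn from the trial will not be replaced and will not be followed-up". The second is "Subjects who drop out of the trial will be followed up according to the intention-to-treat principle".

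The section Definition of treatment adherence and dropout defines the second group: "A patient is considered a dropout, if the patient actively informs the therapist that the patient wishes to stop treatment". A patient who merely goes silent is not a dropout and stays enrolled to the end of the 12 weeks.

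Statistical methods describes a modified intention-to-treat analysis in which "all patients with a 3-month evaluation will be analysed as randomised". Table 3 schedules HADS, HeartQoL and EQ-5D-5L at baseline, end of treatment, 6 months and 12 months. Other measures takes health care costs from registers and sets a 12-month horizon for the cost-utility analysis.

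**The concern.** Intention-to-treat needs outcome data on everyone randomised, whatever happens to their treatment. The article applies this to patients who stop by choice but not to those the investigator withdraws on medical grounds. The reason for the missing data is then a health event after randomisation, which may well be related to the outcomes being measured.

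The analysis-set rule compounds this. A patient with no 3-month HADS cannot enter the primary regression, so withdrawal before 3 months removes the patient by rule. A later analysis plan cannot repair it, because it cannot recover questionnaires that were never sent.

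The boundary between the groups is also unclear. *Withdrawn* follows directly on the investigator's power, but it could be read to include patients who leave by their own choice. The dropout definition turns on telling the therapist that one wants to stop treatment. A patient in the usual-care arm has no trial treatment to stop, so the article does not settle whether such a patient who leaves is followed or not. Dropout at 3 months in either arm is itself a secondary outcome, so the unclear definition affects more than missing data.

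**Working it through.** **1. Who loses what.** Combining the withdrawal rule, the analysis-set rule and Table 3:

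| Time of medical withdrawal | Primary analysis (HADS depression, 3 months) | Later HADS, HeartQoL, EQ-5D-5L |
|---|---|---|
| Before 3 months | Excluded: no 3-month evaluation | None collected |
| Between 3 and 6 months | Included | 6 and 12 months lost |
| Between 6 and 12 months | Included | 12 months lost |

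A patient who drops out at any of these times is, by the article's own rule, still followed.

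**2. The plan's sample size.** Inputs from Sample size calculation: difference 2, SD 3.5, power 90%, alpha 0.05 (two-sided assumed), 30% loss.

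- Normal formula: n = 2 × (3.5 × (1.960 + 1.282) / 2)² = 64.4, so 65 per group. The t-test version gives 66 (power 0.903), as stated.
- Inflation: 66 / 0.70 = 94.3. The article states 94 per group, 188 in total. The figures reproduce.

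**3. Effect on power.** With 30% loss, 94 × 0.70 = 65.8 per group are evaluable and power is 0.906. The article does not say whether the 30% includes medical withdrawals. If they come on top, at assumed rates:

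| Extra loss | Evaluable per group | Power |
|---|---|---|
| 2% | 94 × 0.68 = 63.9 | 0.898 |
| 5% | 94 × 0.65 = 61.1 | 0.885 |
| 10% | 94 × 0.60 = 56.4 | 0.859 |

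For a few withdrawals the loss of power is small. The issue is selection, not numbers.

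**4. Possible bias.** Let a share w of an arm be withdrawn, with a mean HADS depression score g points worse than the mean m of those retained. The full arm mean is (1 − w)m + w(m + g) = m + wg, so the retained patients look better by wg. With the same g in both arms, the treatment difference is biased by g times the difference in withdrawal shares. Writing w now for that excess in one arm:

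| Excess w (assumed) | g = 2 | g = 4 | g = 6 |
|---|---|---|---|
| 2% (1.9 of 94) | 0.04 | 0.08 | 0.12 |
| 5% (4.7 of 94) | 0.10 | 0.20 | 0.30 |
| 10% (9.4 of 94) | 0.20 | 0.40 | 0.60 |

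Against the 2-point target this is 0.04 / 2 = 2% to 0.60 / 2 = 30%. An excess in the intervention arm would flatter the intervention; an excess under usual care would work against it. The primary model adjusts for baseline depression and strata, so g should be read as the gap that remains after that adjustment.

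**The case against.** **The two follow-up sentences are compatible.** A reader might infer a flat contradiction. The documents do not support that: the first sentence follows the investigator's power to withdraw, and the second concerns dropouts, whom the article defines as patients asking to stop. These are different groups under different rules. This stands. What remains is that one rule departs from the principle invoked for the other, and that the boundary is loose.

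**Nothing shows that the sickest or costliest patients are lost.** Urgent medical grounds make poorer health plausible, but the article gives no number, severity or cost. On costs it says "Measures of total health care costs measured in EUR will be collected from the Danish administrative health care registers". That needs no patient contact, and nowhere does it say that register data on withdrawn patients are discarded. The article therefore supports no figure for understated costs. This also stands. The questionnaire side of the cost-utility analysis, HeartQoL at 3, 6 and 12 months, would still be lost.

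**The suicidality item is an entry criterion.** Because Table 3 repeats a one-item PHQ-9 at each assessment, a reader might infer that a high score removes patients after randomisation. Eligibility and recruitment lists the threshold among the exclusions, and the ethics section follows it by saying that all others are included. Deterioration during treatment has its own contingency plan, in which removal from the trial is not listed. The item is no part of this point.

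**Differential withdrawal is not shown.** The research team, apart from the treating psychologists, is to be blinded to allocation, which argues against withdrawal depending on arm. On the other side, intervention patients have scheduled calls (weeks 1, 3, 6 and 9) and CORE-10 assessments (weeks 1, 2, 3, 5 and 7), and no such monitoring is described for usual care. Neither consideration settles it, so a difference between arms remains an assumption.

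**The article is a condensed text.** That would excuse silence about follow-up of withdrawn patients. It does not excuse an explicit rule that they are not followed.

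**Conclusion.** The concern holds in a limited form. The article expressly ends follow-up for randomised patients whom the investigator withdraws on medical grounds. With the 3-month requirement, this removes those withdrawn early from the primary analysis, and it costs those withdrawn later their remaining outcomes. It is a departure from intention-to-treat with a risk of selective missing data, and the rule should be changed.

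The size cannot be determined from the article. The range of 0.04 to 0.60 points rests on two assumptions, an excess of 2% to 10% in one arm and outcomes 2 to 6 points worse. If withdrawals are few or balanced between arms with similar outcomes, the bias in the difference is negligible. The sample size is not in question.

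**What to change.** Reconcile Ethics and safety considerations, Definition of treatment adherence and dropout, and Statistical methods:

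- Replace the no-follow-up rule with wording such as: *Stopping the intervention, for any reason including medical ones, does not end data collection. The planned 3-, 6- and 12-month questionnaires and the register data are collected for all randomised patients unless the patient withdraws consent to data collection.*
- Define separately stopping the intervention, withdrawal by the investigator, and withdrawal of consent to data collection. Say how each applies in the usual-care arm and which of them counts towards the dropout outcome.
- Word the analysis set so that a decision to withdraw a patient does not by itself remove that patient from the analysis, and report withdrawals by arm with time and reason.

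The cost is a change of wording, with whatever approval that needs, and a few more questionnaire links. Register data need no patient contact. The required sample size and the clinical handling of patients do not change. At the reported status, 31 of 188 patients had been included, so 188 − 31 = 157 were still to come under the revised rule.
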